# Feasibility of a stepped wedge cluster RCT and concurrent observational sub-study to evaluate the effects of modified ward night lighting on inpatient fall rates and sleep quality: a protocol for a pilot trial

**DOI:** 10.1186/s40814-015-0043-x

**Published:** 2016-01-07

**Keywords:** Falls, Hospital, Feasibility, Randomised trial, Environmental modification, Lighting

## Abstract

**Background:**

Falls among hospitalised patients impose a considerable burden on health systems globally and prevention is a priority. Some patient-level interventions have been effective in reducing falls, but others have not. An alternative and promising approach to reducing inpatient falls is through the modification of the hospital physical environment and the night lighting of hospital wards is a leading candidate for investigation. In this pilot trial, we will determine the feasibility of conducting a main trial to evaluate the effects of modified night lighting on inpatient ward level fall rates. We will test also the feasibility of collecting novel forms of patient level data through a concurrent observational sub-study.

**Methods/design:**

A stepped wedge, cluster randomised controlled trial will be conducted in six inpatient wards over 14 months in a metropolitan teaching hospital in Brisbane (Australia). The intervention will consist of supplementary night lighting installed across all patient rooms within study wards. The planned placement of luminaires, configurations and spectral characteristics are based on prior published research and pre-trial testing and modification. We will collect data on rates of falls on study wards (falls per 1000 patient days), the proportion of patients who fall once or more, and average length of stay. We will recruit two patients per ward per month to a concurrent observational sub-study aimed at understanding potential impacts on a range of patient sleep and mobility behaviour. The effect on the environment will be monitored with sensors to detect variation in light levels and night-time room activity. We will also collect data on possible patient-level confounders including demographics, pre-admission sleep quality, reported vision, hearing impairment and functional status.

**Discussion:**

This pragmatic pilot trial will assess the feasibility of conducting a main trial to investigate the effects of modified night lighting on inpatient fall rates using several new methods previously untested in the context of environmental modifications and patient safety. Pilot data collected through both parts of the trial will be utilised to inform sample size calculations, trial design and final data collection methods for a subsequent main trial.

## Background

Falls are among the most frequently reported adverse events among hospital patients globally [1, 2], with reported rates summarised as ranging from 1 to 9 falls per 1000 bed days [3]. Importantly, approximately 30 % of all falls will result in some level of physical harm to patients [4]. While falls with serious injuries are less frequent [5], these incidents are associated with substantial health system costs [6, 7] and considerable elevation in morbidity and mortality [8, 9]. Falls without injury are also of concern as they can instil a fear of falling among older people [10], which in turn may contribute to future activity limitation and decline in function [11]. Overall, patients who fall in hospital are more likely to experience longer hospital stays [12], poorer outcomes at discharge [13] and require costly care [14]. Hence, prevention of these incidents is an important priority for health facilities.

A range of patient-related or intrinsic factors are known to influence the risk of falls in hospital including advanced age, illness status, functional limitations, cognitive impairments and visual deficits [3, 15, 16]. In addition to these, individual fall events may be also be precipitated by extrinsic variables, such as the presence of slip and trip hazards [5]. Intervention trials have attempted to reduce falls by addressing various modifiable risk factors [4, 17–25], and some have demonstrated effectiveness [4, 17–20]. Yet the inconclusive and negative results yielded by other studies [21–25] highlight the challenges inherent in addressing the problem of falls in the hospital setting. Hospital admissions are typically short; at-risk patients are often acutely ill and present with multiple co-morbidities [26]. As a result, the frequency and intensity of interventions necessary to reverse many patient-level risk factors may be higher than what is feasible in busy and challenging clinical environments. In this regard, targeting the environmental contributors for falls [27–29], specifically through the implementation of environmental redesign measures, could offer some benefits over interventions delivered directly to patients.

In comparison to patient-level intervention strategies, measures involving environmental redesign would be associated with higher initial (fixed) costs but lower ongoing (variable) costs. The initial outlay for environmental modifications may be further lowered if incorporated in routine refurbishments or in the construction of new facilities [30]. More significantly, issues that hamper the delivery of most patient-level interventions, such as fluctuating workloads and competing clinical priorities, would not diminish the effectiveness of environment redesign strategies. Nevertheless, there has been scant research on environmental redesign in the context of fall prevention in the hospital setting and no experimental trials except for one pilot study which evaluated the effects of an environmental redesign intervention (modified flooring) on injuries from falls in hospital wards [31].

### Environmental lighting and the risk of falls among admitted patients

Environmental lighting at night has long been suspected to exert an important influence on the risk of falls among older hospital patients [32] and the prevalence of visual impairment in people aged over 60 [33] is one of the central issues. Age-related deterioration in the visual system is most usually manifested as a loss of visual acuity; however, problems such as reduction in the visual field, lowered sensitivity to luminance contrast, and increased sensitivity to glare are not uncommon [34]. Ageing is further associated with decreasing efficiency in the visual system’s capacity to shift from photopic (normal human vision in brightly lit conditions) to mesopic and scotopic states (vision in transitional and dark conditions, respectively) [35]. While loss of acuity is often correctable, narrowed visual field, degraded contrast sensitivity, increased sensitivity to glare and slower adaptation responses to illumination changes are more difficult to treat. These problems would present challenges for older people as they may be more inclined to ambulate at night [36, 37] and could explain the considerable number of night time inpatient falls that are reported [38].

Recognising the widespread nature of age-related deterioration in visual function, some authors have called for better lighting to reduce falls in older populations [39] and this would equally apply to the design of hospital environments. However, bright lighting in patient rooms at night is generally discouraged by applicable design standards [40]. Yet, patients who ambulate at night may require higher light levels than what is normally provided in sleep environments in order to safely ambulate [41]. In shared patient rooms where both sleep and ambulatory activities may overlap, the disruptive effects of excessive night lighting [42, 43] cannot be ignored. Hence, a more considered approach is necessary when designing night lighting profiles for older hospitalised patients [44].

### Proposed night lighting intervention to reduce falls among admitted patients

A series of completed investigations have examined the effects of various forms of indoor night lighting for older people [45–47]. These studies found that at comparable low illumination levels, indoor lighting systems that enhanced horizontal and vertical (H/V) spatial elements were associated with the highest levels of performance on standardised tests of gait and balance. H/V cues in the above trials were generated through the use of light emitting diode (LED) strips installed in linear arrays around room design features of known dimensions and orientation, specifically the bathroom doorframe. A follow-up field study [48] assessed the suitability of a similar LED-based night lighting scheme to address the issue of insufficient lighting in residential care settings [49] and to assist in fall prevention efforts. The temporary installations consisted of the LED-based H/V lighting as per prior lab trials, but with the inclusion of additional elements to meet the functional lighting needs of older people within the room and bathroom environment [50]. These additional components were targeted illumination (a) within the attached bathroom (in sections above the toilet and sink) and (b) under the resident’s bed to assist residents in finding footwear and to identify hazards in the immediate vicinity of the bed. Illumination levels in various locations within the room were also objectively measured and reported on [51]. The study reported that residents and nursing staff responded positively in post-trial interviews with questions spanning acceptability of the solution and participants’ subjective perception of lighting improvement. Nursing staff also indicated that they would be less likely to switch on overhead lights to conduct patient observations due to the presence of the night lighting. These findings have been integrated into evidence-based recommendations for 24-h variable lighting systems in residential care settings with specific reference to the needs of older people with dementia [52]. The LED luminaires used in this series of research were reported as being of ‘amber’ colour and specifically selected to align with extensive literature on the photobiologic effects of light [43, 53–55] and the perceptual-, health- and mood-related benefits [56, 57] associated with the use of long wavelength light. Notably, the measured illuminance readings from the field trial [48, 51, 58] are within the recommended ranges for patient room night lighting as per Australian and New Zealand Interior lighting standards for hospitals [40].

We hypothesised that the introduction of a LED-based night lighting scheme (the ‘intervention’) in hospital rooms may contribute to fewer falls through several mechanisms (Fig. 1), but primarily through safer overnight ambulation among patients and reduced sleep disruption. We also hypothesised that the intervention would reduce peak lighting levels at night without impeding overnight usage of toilets by patients and would enhance the perceived environment from a patient perspective.

**Fig. 1 Fig1:**
[figure not shown]
Postulated mechanisms of effect via which the night lighting intervention could reduce rates of falls on hospital wards

### Objectives

The primary objective of this pragmatic pilot trial is to understand the feasibility of the stepped wedged cluster randomised controlled trial design to test the effects of introducing modified night lighting across inpatient wards to reduce fall rates. A secondary objective is to study the feasibility of and value gained from a range of proposed data collection methods aimed at understanding the effects of the intervention at the patient level. The pilot data will inform sample size calculations, assist in the confirmation of intervention features, guide the selection of data collection methods and finalise the cost-effectiveness modelling approach to be adopted for a subsequent main trail.

## Methods/design

### Setting

This pilot trial will be conducted in inpatient wards at the Royal Brisbane and Women’s Hospital (RBWH). The RBWH is a 929-bedded publically funded quaternary and tertiary referral teaching hospital in a metropolitan region in southeast Queensland, Australia and is part of the Metro North Hospital and Health Service. A centrally coordinated fall prevention program has been in place at the RBWH for several years, and a consistent approach to fall risk assessment and management is followed across all inpatient wards.

### Design

We will pilot a single-centre-stepped wedge cluster randomised controlled trial (RCT) and a concurrent observational sub-study. The pilot RCT will be aimed at evaluating the effects of the intervention on ward-level fall rates and average length of ward admissions compared to usual care. The mode, quality and quantity of care delivered to patients in intervention wards will not be altered by the pilot trial. The observational sub-study will be conducted with a sample of patients admitted to study wards and will help modelling effects of the intervention on secondary patient- and room-level (environmental) outcomes. The RBWH ethics review board approved this study.

### Design of stepped wedge cluster RCT

The pilot trial will be undertaken across six RBWH wards (or clusters) and will be conducted over a 14-month period. The pilot cluster RCT will be of a ‘stepped wedge’ design [59], which differs in some important respects from the design of a conventional cluster RCT. A stepped wedge cluster RCT has clusters that provide both control and intervention data. This is achieved by implementing the intervention across all clusters recruited to the study. However, the sequence in which wards cross over from one condition to the other is randomly determined. In this study, all of our study wards will commence as controls at baseline. Figure 2 outlines the pattern in which study wards will transition from control to intervention phases. The first ward to transition to intervention phase will do so 2 months after study commencement and subsequent wards will transition to intervention phase at set intervals (or steps) of 2 months until all wards have transitioned from control to intervention phase. A further period of 2 months of data collection will be undertaken before the study is complete. Thus, all wards will provide a minimum of 2 months of control and intervention data. The stepped wedge cluster RCT design described here is increasingly seen as a suitable design for the pragmatic evaluations of patient safety [60, 61] and service delivery [62] interventions.

**Fig. 2 Fig2:**
[figure not shown]
Schematic diagram of study planned progression and trial design

### Wards and participants

We will recruit inpatient wards that are located at the RBWH campus (excluding an off-campus rehabilitation ward) with the highest reported rates of patient falls over the preceding 2 years. No specific limits will be applied to recruitment on the basis of service profile, patient demographics or diagnostic grouping. However, plans for ward closure or major physical refurbishments during the study period will be criteria for non-inclusion due to the potential for confounding effects on the pilot trial. Once study wards have been identified, an independent statistician will generate an implementation sequence using computer randomisation software. The sequence of transition from control to intervention phase will not be revealed en bloc and but rather one ward at a time and 2 months prior to the date of transition. This would mean that the first ward to transition from a control to an intervention phase will be revealed to the study team at baseline (month ‘zero’), with the transition to occur at the start of month ‘two’. Similarly, the second ward to cross over will be revealed at the start of month ‘two’ and cross over at the start of month ‘four’. This advance notification of wards due for transitioning to the intervention phase is necessary to allow adequate time for the hospital building and engineering services to complete and test the installations across all rooms in the ward (shared and single) in time for commencement of the intervention phase. Analysis of fall rates will be at the level of the ward and rely on data aggregated from patient incident reports completed by staff and from data coded routinely from the medical record for all admitted patients. A waiver from seeking individual patient-level consent for this component was sought and granted by the RBWH institutional human research and ethics committee.

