### Sample size

For the cluster RCT, we are constrained by the available funding as to the number of wards that can be included in the pilot trial (six) and period for which data can be collected (14 months), and hence, the overall anticipated sample is estimated to be approximately 7500 patients. While it is more usual for pilot studies to be conducted with smaller sample sizes, physical design change of this nature has never been undertaken within a stepped wedge cluster RCT. Due to the potential of a variety of operational and logistical challenges in installing new equipment over entire wards, we anticipate that the feasibility of such an approach will only be confirmed by undertaking a rolling sequence of ward installations. In this regard, installations in six wards would provide sufficient opportunities to elicit the full range of practical challenges that may be experienced and afford adequate time to test and modify our implementation approach. Hence, the larger sample size of the study can be considered a secondary feature of this pilot study rather than a primary goal. Within these sample estimates, it is possible to directly calculate the likely effect size that we can detect with 80 % power. Power for parallel cluster randomised trial designs can be calculated by using a conventional power analysis approach and then applying a multiplier to compensate for a design effect, taking the formula [1 + (*n* − 1)**p*], where ‘*n*’ = the number of subjects per cluster and ‘*p*’ = the intra-cluster correlation coefficient to take into account the dependency of observations within clusters [63]. However, the stepped wedge design additionally has a ‘within-cluster’ element (that is, all clusters provide intervention and control data), which provides power advantages to a parallel cluster RCT in a similar way to the comparison of paired with unpaired *t* tests. Hence, a power calculation specific to stepped wedge designs is required. One previously described approach highlights that stepped wedge designs could reduce the required sample size in cluster randomized trials [64], but is based upon the cohort style of stepped wedge design where individual participants are repeatedly measured across the length of the study. This is not consistent with our planned study, which reflects more a cross-sectional style of stepped wedge where individual participants are likely to only have one measurement for their involvement in the study. Fortunately, another power analysis approach based on the cross-sectional style of stepped wedge trial better suited for examining a dichotomous outcome (that is, for comparing patients who fall with those who do not) has been developed [65]. Using this approach, our study has 83 % power to detect an absolute reduction in the proportion of patients who are fallers (patients who experience one or more falls) from 5 % (in control) to 4 % (in intervention) assuming 1071 patients per time period (total *n* ≈ 7500), a coefficient of variation of 0.4, and using six clusters (wards), seven time periods (six steps plus baseline) and a two-tailed alpha of 0.05. This represents a 20 % relative reduction in the proportion of patients who become fallers. We anticipate that the minimum important difference for our intervention is likely to be lower than this since an effect size as low as 5 % relative reduction could still represent a cost-effective solution. Nonetheless, in line with the pilot aims of this trial (primarily focused on feasibility), statistical power and cost-effectiveness are not primary considerations and will be the focus of a subsequent main study if the main aims of this pilot trial are satisfactorily met.

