**Fig. 3 Fig3:**
[figure not shown]
Illustration of in-room locations of lighting intervention and configuration of luminaire installation

RBWH electricians will install the LED lighting units and installations will proceed in fully operational ward environments, without bed closures or patient relocations. The PI will coordinate installations with ward managers to ensure that minimal disruptions to normal work flow occur while ensuring that electricians have adequate access to the ward environment to install and test the lighting and control systems. Output levels of individual luminaires have not been specified in the registered protocol as data of this nature was not available prior to commencement. While it is planned that luminaire output will closely follow output levels specified in prior research [48, 51], further calibration will occur during the installation process in consultation with clinical staff and thereafter left unchanged for the duration of the pilot trial. Resultant luminance (emitted light) will be measured in situ after installations are complete and reported on alongside pilot trial results to assist with replication. Activation of the lighting units will be automated to ensure that they are operational overnight (planned operation from 5 PM through to 7 AM). This will help maximise service life and reduce power consumption. The activation and deactivation times have been selected to ensure availability of the lighting during dark periods and so that local seasonal variations of sunrise and sunset times are accounted for. Importantly, none of the existing lighting will be altered in any way, and staff and patients will have full use of existing lighting in patient rooms and toilets if the installed night lighting was considered inadequate or required supplementation; for example, if additional light is required for patients with severe visual impairment, or if a medical emergency occurs.

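### Lights are fitted, tested and calibrated in occupied wards during time that the analysis counts as control, so part of any installation effect can enter the lighting estimate

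*Protocol article*

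**What the plan says.** All references are to the protocol article.

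- **Wards and participants:** each ward is named two months before it crosses over. The first is named at month zero and crosses at the start of month two. The notice is described as "necessary to allow adequate time for the hospital building and engineering services to complete and test the installations across all rooms in the ward".
- **Design of stepped wedge cluster RCT:** all wards begin as controls, one ward crosses every two months, and "all wards will provide a minimum of 2 months of control and intervention data".
- **Intervention:** lights are fitted in all patient rooms before the ward enters its intervention phase. After Fig. 3 the section adds that "installations will proceed in fully operational ward environments, without bed closures or patient relocations" and that "further calibration will occur during the installation process in consultation with clinical staff".
- **Statistical analysis:** the fixed part of the falls models contains group (intervention or control phase), time period and a covariate for earlier falls on the ward. No installation or transition state is named.
- **Elsewhere:** planned major refurbishment excludes a ward because it might confound (Wards and participants). Staff are to be asked about disruption from the installations, but only after the trial (Post-implementation staff surveys).

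**The concern.** Taken together, these sections put the building work into the last control period of every ward, while the analysis treats that period as ordinary care. Two mechanisms are plausible, with opposite signs. Work in occupied rooms might raise falls or their reporting; the control phase would then look worse and the lighting better. Alternatively, lights switched on for testing, or extra staff attention, might lower falls before crossover and hide part of a real benefit. The article documents neither mechanism.

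The position of these cells matters. They lie on the diagonal of the design, next to crossover, where a stepped wedge analysis puts substantial weight, and adjustment for calendar period does not remove an effect that moves from ward to ward. For the first ward the overlap is complete: its only control period is also its installation window.

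At stake is the direction of effect that the pilot will report, the economic model that is to inform progression, and whether the main trial copies a layout with no separate installation phase.

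**Working it through.** **Inputs (Sample size section).** Fallers 5% in control and 4% in intervention; six wards; seven periods; coefficient of variation 0.4; "a two-tailed alpha of 0.05"; "assuming 1071 patients per time period". Spread over six wards, this is 1071/6 = 178.5 patients per ward-period. Over seven periods, 7 × 1071 = 7497, which agrees with the statement that "the overall anticipated sample is estimated to be approximately 7500 patients".

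**Model.** Cross-sectional stepped wedge linear mixed model on ward-period proportions, with fixed period effects and a random ward effect. Cell variance = 0.045 × 0.955/178.5 = 0.000241. Between-ward SD = 0.4 × 0.05 = 0.02. This approximates the planned logit and negative binomial models and leaves out the earlier-falls covariate.

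**The plan's own figure.** The plan states 83% "power to detect an absolute reduction in the proportion of patients who are fallers". At 178.5 patients per ward-period the SE of the effect is 0.0083 and power is 23%. A figure near 83% (82.6%) appears only with 1071 patients in every ward in every period, about 45,000 in all. That is a separate matter; here I carry both sizes to show that the result does not depend on it.

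**Exposed cells.** The wards have 1, 2, 3, 4, 5 and 6 control periods: 1 + 2 + 3 + 4 + 5 + 6 = 21. One per ward is the notice window: 6/21 = 29%. This is all of the first ward's control data, half of the second's and one sixth of the last's.

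**Weight on those cells.** The estimator is a weighted sum of the ward-period proportions. Weights sum to +1 over intervention cells and −1 over control cells. For the six pre-crossover cells, first ward to last:

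−0.093 − 0.103 − 0.113 − 0.123 − 0.133 − 0.143 = −0.708

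The sum is −0.74 at 1071 per ward-period, and −0.43 at 178.5 with no between-ward variance.

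**Bias.** Bias = (sum of weights) × (share of window occupied) × (installation shift). For a rise in fallers above 5.0%, all assumed:

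| Shift during works | Whole window | Half | Quarter |
|---|---|---|---|
| +0.5 points (10% relative) | −0.35 | −0.18 | −0.09 |
| +1.0 points (20% relative) | −0.71 | −0.35 | −0.18 |

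Entries are percentage points in the lighting effect; the planned effect is −1.0. At 1071 per ward-period the first entry is −0.37. Signs reverse if falls drop during installation: effective lights lit for half of each window would hide 0.708 × 0.5 × 1.0 = 0.35 points.

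**Cost of modelling it.** An indicator for the full two months raises the SE from 0.0083 to 0.0103 (+24%). Excluding the six cells gives about the same SE, 0.0103, lowers power from 23% to 16%, and leaves the first ward with no control data.

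**The case against.** A reader might infer that every window is filled with building work, that the first ward has no clean control data, and that installation effects pass one for one into the estimate. The article does not support this. Two months is a notice period, and no duration of works is given. The job is strip lighting at three toilet and basin locations, not the major refurbishment that excludes a ward. The pass-through is about 0.7 even when the whole window is affected. Nothing says that lights are left on before crossover. These objections stand, and the figures above are upper-end for that reason.

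A reader might also call the statement about two months of control data false. It is true under the protocol's own definition, since the ward has not yet crossed over; it is silent on whether those data are undisturbed.

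There is mitigation. The principal investigator coordinates the works to limit disruption, and the secondary analysis of falls between 7 PM and 6 AM would be less exposed if works are done by day, although working hours are not stated.

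An installation term can also cost more than it saves. In the 0.5-point example, squared bias is 0.00354² = 1.3 × 10⁻⁵, while the added variance is 0.01027² − 0.00826² = 3.7 × 10⁻⁵. A full-window term lowers mean squared error only if the shift exceeds √(3.7 × 10⁻⁵)/0.708, or about 0.86 points. This argues against changing the primary model.

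Finally, sensitivity analyses are usually left to an analysis plan, and this is a feasibility pilot in which testing is not the main purpose. That lowers the weight of the point but does not remove it: the overlap for the first ward is set by the design, and no later analysis can recover work dates that were never logged.

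**Conclusion.** The point holds in a limited form. Installation, testing and calibration in occupied wards fall within control time, and the analysis has no state for them. Up to 6 of 21 control ward-periods are exposed, including the whole of the first ward's control phase. Under the linear approximation about 0.7 of a full-window effect enters the lighting estimate with opposite sign (0.43 to 0.74 across the settings tried), and proportionally less if works fill part of the window. In the 0.5-point example the bias is about 0.43 of one SE (0.0035/0.0083). Whether there is any installation effect, in which direction and for how long, is unknown from the article. It is a cheap improvement rather than a flaw that invalidates the pilot, and it serves the stated aim of learning whether rolling installations suit this design.

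**What to change.** 1. For each ward, log the start and end of works and every period of test or calibration lighting.
2. State that units stay off until the scheduled crossover, except for logged tests.
3. Keep the two-state model as primary. Pre-specify one sensitivity analysis for the falls outcomes in which logged installation time is a third state in the fixed part of the model.
4. In Design of stepped wedge cluster RCT, note that the first ward's control data overlap its installation window.
5. Report the logged durations and the sensitivity result, so that the main trial can decide whether it needs a separate installation phase.

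The cost is a work log and a few sentences. Precision is lost only in the sensitivity analysis: its SE is up to about 24% larger if the full window is flagged, and less if only actual work dates are.
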